#### Incentives

Modest incentives were given to participants for completing assessments in the study. Participants in the intervention group could be compensated up to US $140 when completing all assessments over the nine-month study period. Participants in the waitlist-control group were compensated up to US $190 when opting to use the intervention app after nine months, and US $140 if they chose not to use the intervention app. All consenting participants who completed in-person site visits, baseline visits, and nine-month follow-up were compensated US $50, and an additional US $20 for each remotely completed follow-up survey (immediately postintervention, after three months, and after six months). Waitlist-control participants who opted to use the intervention app were eligible for an additional US $50 postintervention follow-up assessment incentive.

### Measures

#### Serostatus-Specific Measures

##### HIV-Negative Participants

For HIV-negative participants, HIV testing was assessed at baseline using a series of questions about HIV screening in the previous 12-month and three-month intervals, including reasons for screening behavior. Follow-up surveys asked about HIV screening behaviors in the past three months. HIV-negative participants were also asked a series of questions related to PrEP, including if they were aware of PrEP, had ever used PrEP, were currently using PrEP, or had discontinued PrEP. Reasons for use or nonuse of PrEP were also included at baseline and in three-month follow-up intervals. HIV-negative participants were also asked about the likelihood of using possible PrEP agents in the future. Additionally, participants were asked to rank their prevention preferences when considering PrEP options that might be available as future PrEP formulations.

##### HIV-Positive Participants

Participants living with HIV were asked at baseline about their previous 12 months of engagement with HIV care, and at follow-up about their previous 3 months of engagement with HIV care. Questions included missed appointments, reasons for nonengagement, and measures of viral suppression. Participants living with HIV were also asked at baseline about their use of ART in the previous 12-month period and previous 30-day adherence. Postintervention surveys asked about previous three-month initiation of ART and past 30-day adherence to ART, if applicable. Questions also included reasons for missed doses as well as the HIV Self-Efficacy Adherence Scale [28].

#### Questions Asked of All Participants

STI testing was assessed at baseline by asking participants if they had been screened in the previous 12-month period for non-HIV STIs, reasons for screening behavior, and any STI-related vaccinations. STIs for analysis included chlamydia, gonorrhea, syphilis, herpes, genital warts, hepatitis A, B, and C, and any other STI. Follow-up surveys asked information about screening and diagnoses in the previous three months. All participants were asked at baseline and in follow-up surveys about their recent experiences in accessing health care. All participants were asked about their beliefs on the efficacy of various HIV prevention methods (eg, condoms, PrEP) as well as the likelihood they would engage in HIV prevention behaviors in the next three-month period. All participants were asked about sexual behaviors in the previous three-month period at baseline and during three-month follow up surveys. Questions delineated main from casual partners, enumerating casual partners, and determining patterns of behavior for ongoing risk group classification. Participants were asked at baseline and in all postintervention surveys about substance use and dependency. Alcohol misuse was assessed using the validated Alcohol Use Disorders Identification Test (AUDIT) [29]. Participants were also asked which, if any, substances other than alcohol they used. Substance dependency was assessed with the Drug Use Dependency Identification Test (DUDIT) [30].

#### Covariates

Factors that might be associated with intervention efficacy were assessed at baseline and at three-month intervals. These included the Centers for Epidemiological Studies on Depression 10-item (CESD-10) scale [31] for past-week depressive symptoms, a modified technology use scale from a 2015 Pew report [32], lifetime and previous three-month sex work, previous three-month intimate partner violence (IPV), previous-month resilience, a subset of items from the HIV-related Stigma Scale, a modified HIV/AIDS Conspiracy Scale [33], Perceived HIV Severity Scale [34], and Health Care Mistrust Scale [35].

### Data Analysis Plan

We will conduct bivariate analyses, stratified by intervention group, for characteristics related to demographic factors, educational history, social determinants of health, city of enrollment, risk group, and baseline behaviors, to assess for failure of randomization. Failure of randomization will be defined by a significant (*P*<.05) difference in the distribution of a characteristic between the intervention and control groups.

The primary outcomes of interest in this study (Table 2) will be associated with the following alternative hypotheses: assignment to the intervention group will be associated with increased HIV testing among HIV-negative men, increased engagement with HIV care and ART use/adherence among people living with HIV, increased uptake and adherence to PrEP among higher risk HIV-negative men, sustained lack of condomless anal sex among lower risk HIV-negative men, increased condom use for those who reported prior condomless sex, and increased STI testing for all sexually active men. Assuming that there are no failures of randomization, we will use descriptive analyses to calculate the ratios of rates or prevalence between participants assigned to the intervention group and participants assigned to the control group. For HIV testing, PrEP uptake, and STI testing, we will consider using descriptive methods for time-to-event analysis and describing unadjusted hazard ratios if randomization does not fail. If a failure of randomization occurs, we will conduct a stratified analysis for the association between outcomes and randomization assignment by variable where the failure occurred and will consider adjusting estimates for that factor if indicated.

**Table 2 table2:** Primary outcomes.

Outcome	Participant HIV risk group	
	Lower risk and higher risk HIV-negative	HIV-positive
HIV testing	✓	
Engagement in HIV preventative care	✓	
PrEP^a^ uptake	✓	
PrEP adherence	✓	
Engagement in HIV care		✓
ART^b^ uptake		✓
ART adherence		✓
Condom use	✓	✓
Condom use compliance	✓	✓
STI^c^ testing	✓	✓

^a^PrEP: pre-exposure prophylaxis.

^b^ART: antiretroviral therapy.

^c^STI: sexually transmitted infection.

Secondary outcomes will focus on participants’ self-reported intentions, such as increasing the frequency of preventive behaviors, decreasing risk behavior, seeking information and treatment, and partner communication, particularly around risk and prevention behaviors such as ART and PrEP. Secondary outcome analysis will include intervention and control group comparisons, similar to primary outcome analysis.

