Our study is subject to a number of possible limitations, typical of the potential biases associated with randomized prevention trials [38]. It is possible that we might have selection bias, manifested as a failure of randomization. We have taken steps to mitigate this possibility by implementing stratified randomization by site and risk group; stratified randomization minimizes the risk for failure of randomization across a domain that might be associated with efficacy. We will assess failure of randomization by comparing the distribution of key participant characteristics by randomization arm, using chi-square or Fisher exact tests as appropriate. We anticipate that there could be measurement bias because we are relying on self-reported outcomes, as is common in behavioral studies. We have attempted to minimize this bias by allowing options for completing assessments privately or remotely, by using previously established or validated items, and by measuring key outcomes with multiple measures (for example, adherence is assessed in both 7-day and 30-day recall periods, and assesses condom use in the past 3 months and at last sexual encounter). We could be subject to exclusion bias if there is differential loss to follow-up between the intervention and control arms. We mitigated this risk by using proven approaches to increase retention in both arms, including multiple modes of contact (phone, email, text message) and offering flexible options for completing surveys at home or in the research clinic. Because we set quotas to ensure adequate representation of men of color and high- and low-risk HIV-negative men, our sample may not have high external generalizability; however, we have designed the study to have power to analyze within specific, high-priority groups of participants, given their importance in HIV epidemics among MSM living in the United States. Because of the recruitment structure, cross-sectional analyses of the levels of prevention and risk behaviors from the baseline data should be interpreted in light of the sampling strategy.

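### A P<.05 test of baseline differences is used to declare randomization failed and to choose the primary analysis; overall type I error is not inflated, but the primary estimate becomes data-dependent

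*Protocol article*

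**What the plan says.** The Data Analysis Plan compares the arms on "characteristics related to demographic factors, educational history, social determinants of health, city of enrollment, risk group, and baseline behaviors, to assess for failure of randomization". It then sets the rule: "Failure of randomization will be defined by a significant (*P*<.05) difference in the distribution of a characteristic" between the arms.

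The result decides the analysis of the primary outcomes:

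- **Nothing flagged:** "Assuming that there are no failures of randomization, we will use descriptive analyses to calculate the ratios of rates or prevalence" between arms. For HIV testing, PrEP uptake and STI testing, unadjusted hazard ratios are also to be considered.
- **Something flagged:** "we will conduct a stratified analysis for the association between outcomes and randomization assignment by variable where the failure occurred". Adjustment for that factor is then to be considered if it seems indicated.

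The Discussion repeats the check on key characteristics, "comparing the distribution of key participant characteristics by randomization arm, using chi-square or Fisher exact tests as appropriate", and describes the risk as "selection bias, manifested as a failure of randomization".

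The Randomization section says that men were allocated 1:1 from randomly permuted blocks of 2 and 4, within 18 strata formed by serostatus/risk group, city and race/ethnicity.

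**The concern.** If the allocation was carried out as described, the null hypothesis of every baseline test is true. A result below .05 is then a chance finding. It is evidence neither of failed randomization nor of selection bias. City and risk group are on the test list but are also stratification factors, so their tests will almost never be significant. The flags would come from the other characteristics.

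The P-value is also the wrong criterion for adjustment. It measures imbalance against sample size and ignores the variable's relation to the outcome. A variable unrelated to any outcome can trigger the switch, while an imbalance at P=.06 in a strong predictor, such as past HIV testing, triggers nothing.

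At stake is whether a reader can know in advance which estimate is primary for the outcomes in Table 2. The secondary outcomes are affected too, because they follow a similar analysis.

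**Working it through.** The article gives no figure on this point to reproduce. The inputs from it are the .05 threshold, 1:1 allocation and 1229 men (478 + 335 + 416), taken here as 615 and 614 per arm on the assumption of an even split. The number of characteristics, k, and the baseline-outcome correlation, r, are not given. Both are assumed and shown over a range.

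**1. Chance of at least one false failure.** For independent tests this is 1 − 0.95^k:

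| k | 6 | 10 | 14 | 20 | 30 | 40 |
|---|---|---|---|---|---|---|
| Chance | 26% | 40% | 51% | 64% | 79% | 87% |

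Baseline characteristics are usually correlated. Simulation with pairwise correlation 0.5 to 0.2 gives 21% to 25% for k=6 and 42% to 59% for k=20.

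**2. Imbalance that escapes the rule.** The largest difference in proportions that stays above P=.05 is 1.96 × √[p(1−p)(1/615 + 1/614)]. This is 3.4 percentage points at p=0.10, 4.5 at p=0.20 and 5.6 at p=0.50. In an illustrative subgroup of 100 per arm it is 11.1 points at p=0.20 and 13.9 at p=0.50. Subgroups matter because several primary outcomes apply to only some of the risk groups.

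**3. Error conditional on one unflagged imbalance.** Take a baseline imbalance of z=1.9 (P=.057) and no treatment effect. The unadjusted outcome statistic is then distributed N(1.9r, 1−r²). The probability that it exceeds 1.96 in absolute value is:

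- r=0.4: mean 0.76, SD 0.917, 9.7%
- r=0.5: mean 0.95, SD 0.866, 12.2%
- r=0.6: mean 1.14, SD 0.800, 15.3%

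The same formula with z=0 and r=0.5 gives about 2.4%, below nominal. The direction therefore depends on the imbalance that happens to arise.

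**4. Overall error and power.** These come from a simulation of 400,000 draws with one baseline covariate. Power is set where the unadjusted test has 80%, using a linear-model approximation.

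| r | Type I error, test then adjust | Type I error, always adjust | Power, always adjust |
|---|---|---|---|
| 0.3 | 4.8% | 5.0% | 84% |
| 0.5 | 4.3% | 5.0% | 90% |
| 0.7 | 3.6% | 5.0% | 98% |

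When the baseline P lies between .05 and .10, the unadjusted test has error of 7%, 11% and 16% for r=0.3, 0.5 and 0.7. The adjusted test stays at 4.8% to 5.0%.

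**The case against.** The strongest reply is that an unadjusted comparison in a randomized trial is valid. Averaged over allocations it is unbiased and holds its 5% level, and the test-then-adjust rule comes out slightly below 5%. This stands. A reader might infer from step 3 that the plan's type I error is about 12%, or that its estimates are biased. The documents do not support either: the 12% is conditional on one chosen imbalance and an assumed r.

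A reader might also infer that this trial would probably be reported as a randomization failure. That needs about 14 or more independent tests. The article gives no count, and the Discussion speaks only of key characteristics.

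Three narrower replies also stand in part:

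- The article writes unadjusted only for hazard ratios. For prevalence and rate ratios it is implied, because descriptive analyses are named without covariates.
- Adjustment after a flag is only to be considered, so adjusting for an irrelevant variable is possible but not required. This softens the rule but adds discretion, since the stratified analysis is still triggered.
- Risk group is defined by condomless anal sex and PrEP use, and randomization was stratified by it. That composite is thus closely balanced among HIV-negative men. Condom use among HIV-positive men, the separate components within the lower-risk group, and behaviours such as testing are not covered.

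Finally, covariate lists are commonly left to an analysis plan, and their absence here is not the point. The point is a rule that the article itself states.

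**Conclusion.** The concern holds, with its harm properly limited. The plan lets chance baseline differences decide which primary analysis is run, and it labels such differences a failure of randomization. The chance of at least one false label runs from about one in five (6 correlated characteristics) to 79% (30 independent ones); both counts are assumptions.

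The costs are a data-dependent primary estimate, precision given up when nothing is flagged, a misleading public statement about the randomization, and a conditional error of about 10% to 15% at z=1.9 for r of 0.4 to 0.6. Inflated overall type I error is not among them. The conclusion assumes that allocation was carried out as the Randomization section describes. The power figures are illustrative.

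**What to change.** Delete the P<.05 definition and the switch that depends on it. Report baseline characteristics by arm descriptively, without tests.

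Before analysis, fix one model for each primary outcome, containing:

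- arm;
- the stratification factors that vary in that outcome's population: city, race/ethnicity, and risk group where more than one group is included;
- the baseline value of the outcome, or its nearest baseline measure, where one exists and is not constant by definition.

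The last item must be settled outcome by outcome. Higher-risk men are by definition not taking PrEP as prescribed at baseline, so baseline PrEP adherence carries little information for them. Sustained absence of condomless sex presupposes none at baseline. STI testing and HIV care are recalled over 12 months at baseline but over 3 months at follow-up, so the 12-month item would serve as the nearest measure.

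Use each model whatever the baseline table shows, with the unadjusted ratio as a sensitivity analysis. Reword the Discussion so that chance imbalance is not called selection bias.

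The chance that baseline P-values change the primary analysis then falls to zero. The cost is the work of specifying covariates for each outcome. No new data are needed, because the stratification factors and baseline behaviours have been collected.

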## Introduction

### Background

Men who have sex with men (MSM) face the highest burden of HIV in the United States [1], and there is a paucity of efficacious or promising mobile health (mHealth), HIV-prevention interventions tailored specifically for MSM [2]. New HIV prevention tools are needed that can address the needs of MSM, especially young MSM aged 15-24 for whom yearly HIV incidence doubled from 2002 to 2014 [3], and for young MSM of color for whom these burdens are most severe [4-6]. Currently, HIV prevention services are underutilized by MSM, with just over half (56%) reporting being tested in the past 12 months, high proportions (76% of HIV-positive and 66% of HIV-negative MSM) reporting recent condomless, receptive anal intercourse, and few (<20%) reporting utilization of pre-exposure prophylaxis (PrEP) [7]. Statistical models of MSM epidemics parameterized to represent US epidemics demonstrate that high levels of prevention service coverage will be required to substantially reduce HIV incidence [8,9], and increased utilization of routine prevention activities, like frequent HIV testing, may enhance the uptake of biomedical interventions like PrEP [10]. At the same time, engaging MSM living with HIV in mHealth HIV-prevention efforts is critical and addresses the two most important factors that determine cost-effectiveness, namely the HIV prevalence of the target population and the cost per person reached [11].

Researchers in the past decade have been exploring the most effective ways to engage MSM in a package of HIV prevention services. A growing body of research has suggested that mobile phone apps provide a dynamic environment for intervention and can offer on-demand prevention services for MSM [12-17]. This research indicates that MSM are open to receiving prevention information and resources via apps [18]. Electronic messages communicated through apps, known as mobile messaging, are an appealing approach to enhance intervention uptake because they allow for messaging that can reach a wide audience of MSM, including rural MSM [16]. Further, younger MSM might be especially interested in using mobile technology to receive health information [19]. This study builds on an existing HIV prevention app designed for MSM, HealthMindr, to add and evaluate tailored prevention messaging.

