## Methods

### Overview

The Mobile Messaging for Men (M3) study was conducted in two phases. The first phase consisted of a series of focus groups and in-depth interviews to ensure that written messages, videos, and app features presented in the trial were appropriate for the audience. The second phase was an RCT, with MSM in three serostatus/risk groups randomized to receive either the intervention condition (M3 app) for a three-month exposure period or a waitlist-control condition with the option to receive the app for three months at the end of the study. The serostatus/risk groups were defined by self-report as: (1) HIV seropositive; (2) HIV seronegative at higher risk (condomless anal sex and not taking PrEP as prescribed in the past 3 months); and (3) HIV seronegative at lower risk (no condomless anal sex in the past 3 months, or condomless anal sex while taking PrEP as prescribed in the past 3 months). Postintervention data collection occurred at three time points: 3 months (immediately postintervention), 6 months (three-months postintervention), and 9 months (six-months postintervention) (see Figure 1). Participant follow-up will be completed in September 2019, with primary outcome analyses to follow. The study was reviewed and approved by the Emory University Institutional Review Board (Protocol #87684) and registered at ClinicalTrials.gov (NCT03666247).

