### Formative Research for Online Messages

#### Message Development Process

Message development for qualitative input from the target audience took two forms: brief written message and video message development. Two committees of subject matter experts (written messages: [name]; video messages: [name]) were established to implement written and video message creation. First, the committees determined six domains of prevention messages and related study outcomes: (1) condom use; (2) HIV testing; (3) STI testing; (4) PrEP continuum outcomes; (5) antiretroviral therapy (ART) use; and (6) engagement in care.

The written message committee reviewed the literature on HIV prevention messages in the six domain areas, as well as messages used in their ongoing research, and developed 63 messages that were 2-3 sentences each and were organized into the 6 prevention domains. Messages within each domain were mapped onto Social Cognitive Theory constructs (eg, information, relevance, norms, barriers, and self-efficacy). Through the mobile app, each participant received a common core of 36 messages (approximately 6 messages per domain) and another set of 9 secondary messages specific to each of the 3 serostatus/risk groups. For HIV-positive men, these secondary messages focused on ART uptake and adherence, for HIV-negative men who reported condomless anal sex in the past three months, additional messages pertained to PrEP, and for HIV-negative men who did not report recent condomless anal sex, additional messages were about condom use and HIV/STI testing. Participants were sent a written message every 1-2 days and a video message once per week.

The video messages were selected after identifying existing videos in the field of recent HIV and STI prevention related to the six domain areas, with the goal of identifying 12, approximately one-minute video clips for delivery on the mobile app. About two videos per domain area were delivered to all study participants at a rate of one per week. Through online searches and common, prevention video–development funding agencies (eg, the Centers for Disease Control and Prevention and the Kaiser Family Foundation), an initial pool of several hundred videos was identified, and they were systematically and iteratively reduced in number by the subject matter expert committee through several rounds of reviews and ratings.

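### The hypothesis of sustained absence of condomless sex is set for a stratum that, by definition, includes men having condomless sex on PrEP at baseline

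*Protocol article*

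**What the plan says.** The Overview of the Methods sorts HIV-negative men into two groups by self-report. Higher risk means "condomless anal sex and not taking PrEP as prescribed in the past 3 months". Lower risk means "no condomless anal sex in the past 3 months, or condomless anal sex while taking PrEP as prescribed in the past 3 months". The label is a formal stratum: under Randomization, the serostatus/risk group is one of the three stratification factors.

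The Data Analysis Plan attaches hypotheses to the primary outcomes. Two concern condoms: "sustained lack of condomless anal sex among lower risk HIV-negative men" and "increased condom use for those who reported prior condomless sex". The first names the stratum and places no condition on baseline behaviour. The second names a behaviour and places no condition on risk group. The comparison is to be a ratio of rates or prevalences between arms.

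On data, Questions Asked of All Participants states: "All participants were asked about sexual behaviors in the previous three-month period at baseline and during three-month follow up surveys".

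The Message Development Process describes the third secondary-message group differently: "for HIV-negative men who did not report recent condomless anal sex, additional messages were about condom use and HIV/STI testing".

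**The concern.** A sustained lack can be seen only in someone who starts with the lack. A man classed as lower risk through the PrEP route reported condomless sex in the three months before baseline. If he reports none at follow-up, that is a change in behaviour, not maintenance. The population named in the hypothesis therefore does not fit its outcome.

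The same man has reported prior condomless sex and so also belongs to the second condom hypothesis. Nothing in the text takes him out of the first. At stake is a primary comparison whose denominator includes men it was not designed for. Most of them would be expected to report condomless sex in both arms, which would dilute any effect in the men for whom maintenance is a meaningful goal.

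**Working it through.** **Definitions side by side.**

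| Baseline behaviour, HIV-negative men | Stratum (Overview) | Sustained-lack hypothesis | Increased-condom-use hypothesis |
|---|---|---|---|
| No condomless sex | Lower risk | Yes | No |
| Condomless sex, PrEP as prescribed | Lower risk | Yes, by label | Yes, by behaviour |
| Condomless sex, not on PrEP as prescribed | Higher risk | No | Yes |

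The middle row is the problem.

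**No stated figure to reproduce.** The article gives no sample size calculation, effect size or event rate for this outcome, and neither the size of the lower-risk stratum nor its PrEP-route share. Everything below is illustration on assumed inputs.

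**Plausible share of PrEP-route men.** Share = P(condomless and PrEP) / [P(none) + P(condomless and PrEP)]. The Background cites "high proportions (76% of HIV-positive and 66% of HIV-negative MSM) reporting recent condomless, receptive anal intercourse" and PrEP use below 20%. Take 66% for condomless sex and 5% to 20% for PrEP use.

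- Independent: 0.033/(0.34 + 0.033) = 9%, up to 0.132/(0.34 + 0.132) = 28%.
- Every PrEP user has condomless sex: 0.05/0.39 = 13%, up to 0.20/0.54 = 37%.

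These figures are rough. The 66% covers receptive sex only, taking PrEP as prescribed is narrower than any use, and recruitment used quotas.

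**Dilution.** Assume 205 lower-risk men per arm (about one third of 1229, split 1:1), condomless sex at follow-up of 25% (control) and 15% (intervention) in men with none at baseline, and 90% in both arms in PrEP-route men. With share s, the whole-stratum rates are (1 − s) × 0.25 + 0.9s and (1 − s) × 0.15 + 0.9s. Power is for a two-sided 5% test of two proportions; the restricted analysis has 205 × (1 − s) men per arm.

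| s | Control vs intervention | Risk difference | Ratio, condomless sex | Ratio, lack of it | Power, whole stratum | Power, intended men only |
|---|---|---|---|---|---|---|
| 0 | 25.0% vs 15.0% | 10.0 points | 0.60 | 1.133 | 72% | 72% |
| 10% | 31.5% vs 22.5% | 9.0 | 0.71 | 1.131 | 54% | 67% |
| 20% | 38.0% vs 30.0% | 8.0 | 0.79 | 1.129 | 40% | 62% |
| 30% | 44.5% vs 37.5% | 7.0 | 0.84 | 1.126 | 30% | 56% |
| 37% | 49.1% vs 42.8% | 6.3 | 0.87 | 1.124 | 25% | 52% |

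The restricted analysis has fewer men and still more power at every share above zero.

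**A second set of assumptions.** Let lack of condomless sex be 60% vs 74% in the intended men and let PrEP-route men never show it. At a 10% share, power is 74% in the whole stratum against 82% restricted; at 30% it is 51% against 72%. The risk difference falls from 14 points to 14 × 0.7 = 9.8 at a 30% share. The ratio does not change: 0.518/0.42 = 0.74/0.60 = 1.23.

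**Secondary messages.** The Message Development Process divides HIV-negative men by condomless sex alone and gives those reporting it additional PrEP messages. Table 1 shows no secondary PrEP messages for the lower-risk group. A PrEP-route man falls on different sides of these two descriptions.

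**The case against.** The strongest reply is that the word sustained already presupposes no condomless sex at baseline and that the next clause picks up everyone else. Read together, the two clauses would split men by baseline behaviour, and exact analysis sets are commonly left to a fuller document. That may well be the intent, and no sentence says that PrEP-route men will be analysed twice. But the first clause names a defined stratum that is also a randomization factor, and that definition includes these men. This is a stated population that does not fit its outcome, not a detail left out.

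Three stronger readings are tempting, and the documents do not support them.

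- *A true ratio of 0.60 would be reported as 0.84.* That is the ratio for having condomless sex, the complement of the stated outcome. For lack of condomless sex the same inputs give 1.133 against 1.126.
- *Many lower-risk men are affected.* The article gives no count. The cited background rates make roughly 9% to 37% conceivable, no more than that.
- *The comparison is biased.* Randomization was stratified by risk group, and PrEP-route men should be balanced between arms in expectation, though route of entry was not itself a stratification factor.

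Two further replies stand in part. The article calls the primary comparison descriptive, so the power figures presuppose a test that it does not specify; the loss of precision does not depend on that. The message wording may be shorthand, because Intervention Messaging says that delivery followed risk group assignment, updated by check-ins. In any case it does not alter the analysis set.

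**Conclusion.** The point holds at moderate severity. As written, a primary condom hypothesis covers men who cannot meet its premise, and its population overlaps with that of the neighbouring hypothesis. The consequence is a smaller risk difference, lower power and an ill-defined population. It is not between-arm bias, and the ratio for the outcome as stated is nearly unaffected.

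On the main set of assumptions, including these men costs about 13 percentage points of power at a 10% share (54% against 67%) and about 26 at a 30% share (30% against 56%). These figures rest on an assumed stratum size, assumed event rates and an undocumented PrEP-route share. They show direction and rough scale, not the loss in this trial.

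**What to change.** Define the two condom analysis sets by reported baseline behaviour instead of the stratum label.

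1. Sustained absence of condomless anal sex: HIV-negative men reporting none in the three months before baseline.
2. Increased condom use: men reporting condomless anal sex at baseline, including those classed as lower risk through PrEP. Alternatively, report the PrEP-route men separately as a secondary analysis.
3. State the number of PrEP-route men in each arm, so that readers can see how much the choice matters.

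Separately, reconcile the Message Development Process with the Overview, Intervention Messaging and Table 1 on which rule assigned the secondary messages.

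The cost is a change of wording. Three-month sexual behaviour was collected at baseline from all participants, so no new data are needed. The small downside is a smaller denominator for the first set.
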